### **9.3.7 AMA-1 sequencing and genotyping**

To the extent that the vaccine effect is allele-specific, we hypothesize that the frequency of malaria infections with AMA-1 sequence similar to the 3D7 vaccine strain would decrease in the FMP2.1/AS02A group relative to the control group in a Phase 2 study that is powered for this type of analysis. This Phase 1 trial is not powered to measure efficacy of any type, whether clinical or molecular. However, we may be able to detect trends in frequencies of polymorphisms that will allow us to define specific haplotypes based on particular subsets of the 31 polymorphic amino acid residues that appear to be under selection pressure by the vaccine. These preliminary data will then be used to develop an analysis plan for measuring molecular efficacy in the Phase 2 trial.

At any scheduled or unscheduled visit when clinical malaria is suspected, microscopy for malaria will be performed as a clinical diagnostic procedure for routine medical care. Each time malaria smears are obtained by digital puncture, a few drops (less than 0.2 mL) of blood will be blotted onto

filter paper and preserved for parasite DNA analysis. Unused blood left over after clinical laboratory testing (serum chemistries and CBC) have been done may also be used for parasite genotyping. These samples will be subject to sequencing of AMA-1 to identify polymorphic amino acid residues that may be selected by the FMP2.1/AS02A vaccine and other parasite genotyping studies including microsatellite analysis to aid with characterization of vaccine-resistant strains in future studies. These genotyping studies are expected to guide the development of analytical plans for measuring efficacy at the molecular level in the subsequent Phase 2 trial of this vaccine.

## **10 ASSESSMENT OF SAFETY**

### **10.1 Specification of Safety Parameters**

The primary outcome measures for this trial are:

1. Occurrence of solicited symptoms after each vaccination during a 7-day surveillance period (day of vaccination and days 1, 2, 3 and 7 after vaccination)
2. Occurrence of unsolicited symptoms after each vaccination during a 30-day surveillance period (day of vaccination and 30 subsequent days)
3. Occurrence of serious adverse events throughout the study period

### **10.2 Methods and Timing for Assessing, Recording, and Analyzing Safety Parameters**

#### **10.2.1 Adverse Events**

An adverse event includes any noxious, pathological or unintended change in anatomical, physiological or metabolic functions as indicated by physical signs, symptoms and/or laboratory detected changes occurring in any phase of the clinical study whether associated with the study vaccine or active comparator vaccine and whether or not considered vaccination related. This definition includes an exacerbation of pre-existing conditions or events, intercurrent illnesses, or vaccine or drug interaction. Symptomatic uncomplicated or severe malaria infection will be coded as adverse events as will any other acute illness, throughout the 15 months of the study. Anticipated day-to-day fluctuations of pre-existing conditions that do not represent a clinically significant exacerbation need not be considered adverse events. Discrete episodes of chronic conditions occurring during a study period will be reported as adverse events to assess changes in frequency or severity.

Adverse events will be documented in terms of a medical diagnosis. When it is not possible to make a specific medical diagnosis, the adverse event will be documented in terms of signs and/or symptoms observed by the investigator or reported by the subject at each study visit. Pre-existing conditions or signs and/or symptoms (including any that are not recognized at study entry but are recognized during the study period) present in a participant prior to the start of the study will be recorded on the participant's CRF. Any hospitalization will be considered a serious adverse event. Adverse events to be recorded as endpoints are described below. All other adverse events will be recorded as unsolicited adverse events.

### **10.2.2 Surveillance period for adverse events**

All adverse events occurring within 30 days following administration of each study immunization will be recorded irrespective of severity or whether or not they are considered vaccination-related.

Solicited adverse events will be elicited for a 7-day surveillance period (day of vaccination and study days 1, 2, 3 and 7) and unsolicited adverse events will be recorded during a 30-day surveillance period. Serious adverse events will be recorded throughout the study.

### **10.2.3 Recording adverse events**

At each visit/assessment, the investigator will evaluate all adverse events observed by the investigators or reported by the participant or their parents/guardians. New adverse events will be recorded in the Adverse Event form within the participant's CRF. Solicited and unsolicited adverse events will be recorded on separate pages of the CRF. The nature of each event, date and time (where appropriate) of onset, outcome, intensity and relationship to vaccination will be established. Any corrective treatment will be recorded in the CRF. As a consistent method of soliciting adverse events, the participant and their parents/guardians will be asked a non-leading question such as: "Have you felt different in any way since receiving the vaccine or since the last visit?" The investigator will record only those adverse events having occurred within the time frames defined above.

Adverse events already documented in the CRF, *i.e.* at a previous assessment and designated as 'ongoing' will be reviewed at subsequent visits, as necessary. If these events have resolved, the documentation in the CRF will be completed, including the date that the adverse event resolved. If an adverse event changes in frequency or intensity during a study period, the record will be updated to reflect the maximum intensity or describe the frequency.

### **10.2.4 Solicited adverse events**

#### **Local (injection site) adverse events**

Pain or tenderness at injection site  
Swelling at injection site  
Erythema at injection site

#### **General adverse events**

Fever (body temperature  $\geq 37.5^{\circ}\text{C}$ )  
Drowsiness  
Loss of appetite  
Vomiting  
Irritability/fussiness

Temperature will be recorded at the time of the clinic visit. If additional temperature measurements are recorded at another time of the day, the highest temperature will be recorded.

#### **10.2.5 Unsolicited adverse events**

Unsolicited adverse events will be recorded in the CRF. Unsolicited adverse events are adverse events reported by the participants or accompanying guardians that are different from those solicited symptoms defined in the preceding section and/or that begin after the 7-day surveillance period for solicited adverse events.

### **10.3 Assessment of intensity of non-serious adverse events**

For each solicited symptom the participants and their parents/guardians will be asked if they sought medical advice for this symptom. For all other adverse events than those in Table 11, maximum intensity will be assigned to one of the following categories:

0 = No adverse event

1 = An adverse event which is easily tolerated by the subject, causing minimal discomfort and not interfering with everyday activities.

2 = An adverse event that is sufficiently discomforting to interfere with normal everyday activities.

3 = An adverse event that prevents normal, everyday activities. Such an adverse event would for example prevent normal play or attendance at school and would require the administration of corrective therapy.

Intensity of the following adverse events will be assessed as described in Table 11:

| Table 11. Assessment of Solicited Adverse Event (AE) Intensity |              |                                                           |
|-----------------------------------------------------------------------|--------------|-----------------------------------------------------------|
| AE                                                             | Grade | Intensity Definition                               |
| Pain/tenderness at injection site                                     | 0            | Absent                                                    |
|                                                                       | 1            | Minor reaction to touch                                   |
|                                                                       | 2            | Cries/protests on touch                                   |
|                                                                       | 3            | Cries when limb is moved/spontaneously painful            |
| Swelling at injection site                                            | 0            | Absent                                                    |
|                                                                       | 1            | < 5 mm                                                    |
|                                                                       | 2            | 5-20 mm                                                   |
|                                                                       | 3            | > 20 mm                                                   |
| Erythema at injection site                                            | 0            | Absent                                                    |
|                                                                       | 1            | < 5 mm                                                    |
|                                                                       | 2            | 5-20 mm                                                   |
|                                                                       | 3            | > 50 mm                                                   |
| Limitation of arm motion -
Abduction at the shoulder               | 0            | None                                                      |
|                                                                       | 1            | >90° but <120°                                            |
|                                                                       | 2            | >30° but ≤90°                                             |
|                                                                       | 3            | ≤30°                                                      |
| Fever                                                                 | 0            | < 37.5°C                                                  |
|                                                                       | 1            | 37.5-38.0°C                                               |
|                                                                       | 2            | 38.1-39.0°C                                               |
|                                                                       | 3            | > 39.0°C                                                  |
| Irritability/fussiness                                                | 0            | Behavior as usual                                         |
|                                                                       | 1            | Crying more than usual/ no effect on normal activity      |
|                                                                       | 2            | Crying more than usual/ interferes with normal activity   |
|                                                                       | 3            | Crying that cannot be comforted/ prevents normal activity |
| Drowsiness                                                            | 0            | Behavior as usual                                         |
|                                                                       | 1            | Drowsiness easily tolerated                               |
|                                                                       | 2            | Drowsiness that interferes with normal activity           |
|                                                                       | 3            | Drowsiness that prevents normal activity                  |
| Loss of appetite                                                      | 0            | Normal                                                    |
|                                                                       | 1            | Eating less than usual/ no effect on normal activity      |
|                                                                       | 2            | Eating less than usual/ interferes with normal activity   |
|                                                                       | 3            | Not eating at all                                         |
| Vomiting                                                              | 0            | Absent                                                    |
|                                                                       | 1            | Occasional but able to eat/drink normal amounts           |
|                                                                       | 2            | Repeated with limited oral intake                         |
|                                                                       | 3            | Continuous, unable to keep down liquids or solids         |

| Table 12. Laboratory toxicity grading |                              |               |                |                |                  |
|----------------------------------------------|------------------------------|---------------|----------------|----------------|------------------|
| HEMATOLOGY                            |                              |               |                |                |                  |
|                                              | Normal Range                 | Grade 1       | Grade 2        | Grade 3        | Grade 4
(SAE) |
| Hemoglobin
Male and female                | 8.4 – 12.4 g/dL a | 7.5 – 8.3g/dL | 6.1 – 7.4 g/dL | 5.0 – 6.0 g/dL | < 5.0 g/dL       |

|                           |                                                |                                                                  |                                                                 |                                                                   |                                                |
|---------------------------|------------------------------------------------|------------------------------------------------------------------|-----------------------------------------------------------------|-------------------------------------------------------------------|------------------------------------------------|
| Platelets                 | 133,000 – 523,000/mm  a | 75,000 - 132,999/mm                                  | 50,000 - 74,999/mm                                  | 20,000 - 49,999/mm 
or > 1,000,000/mm  | <20,000/mm                         |
| WBCs                      | 5,300 – 15,300/mm  a    | 15,299 – 16,500/ mm  or 3,501- 5,299/mm  | 16,501- 18,000 /mm  or 2,001- 3,500/mm  | 18,001- 30,000/mm  or 1,000- 2,000/mm     | >30,000 or <1,000 /mm              |
| Absolute Lymphocyte Count | 2,300-9,500/mm  b       | 1,000-2,399/mm                                       | 750-999/mm                                          | 500-749/mm                                            | <500/mm                            |
| CHEMISTRIES        |                                                |                                                                  |                                                                 |                                                                   |                                                |
|                           | Normal Range                                   | Grade 1                                                          | Grade 2                                                         | Grade 3                                                           | Grade 4 (SAE)                                  |
| Creatinine                | 0.2–0.5 mg/dL (15.2–44.2 µmol/L) c  | 44.2 – 91.5 µmol/L (0.5-1.0 mg/dL)                               | 91.6 – 183 µmol/L (1.1-2.0 mg/dL)                               | 183.1 – 366 µmol/L (2.1-4.0 mg/dL)                                | > 366 µmol/L (>4.1 mg/dL) or dialysis required |
| ALT                       | 3.9 – 49.6 U/L a                    | 49.7-124 U/L                                                     | 124.1 – 248 U/L                                                 | 248.1 – 496 U/L                                                   | > 496 U/L                                      |

aDetermined and adapted from normal children in Donéguébougou, a rural Malian village and malaria vaccine trial site

b From Lugada, E. S. et al. Population-Based Hematologic and Immunologic Reference Values for a Healthy Ugandan Population. *Clin Diag Lab Immunol*, 11, 29-34.

c From Current Pediatric Diagnosis & Treatment, 17th edition, 2005.

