### **5.4.3 Reasons for Withdrawal**

The following criteria will be checked at each visit. If any become applicable during the study, the subject will not be required to discontinue the study, but a separate immunogenicity analysis may be done that excludes these individuals.

- Use of any investigational drug or vaccine other than the study vaccine(s) during the study period.
- Chronic administration (defined as more than 14 days) of any dose level of immunosuppressants or other immune-modifying drugs during the study period and chronic daily use of inhaled steroids. Intermittent use of inhaled and topical steroids is allowed.
- Administration of a vaccine not foreseen by the study protocol during the period starting from 30 days before the first study immunization and ending 30 days after the third immunization.
- Administration of immunoglobulins and/or any blood products up to 30 days after the last study immunization.

The following criteria will be checked prior to each immunization and are contraindications to further immunization. However, the study participants and their parents/guardians will be encouraged to continue to participate in the surveillance schedule for safety evaluation.

- Systemic hypersensitivity reaction following administration of the study vaccine. Severe (i.e., Grade III) local reactions will be evaluated to determine whether or not further study immunizations should be administered

Subjects may also withdraw voluntarily from receiving the study intervention upon request for any reason.

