## **10.11 Data Safety and Monitoring Board (DSMB)**

An independent DSMB will be constituted by DMID to review safety data at specified intervals prior to each dose escalation. The role of the DSMB is to provide safety oversight over the conduct of the trial. It will review blinded safety data before each dose escalation and advise on progression to the next dose level. The DSMB will hold two conference calls to review the safety data generated from the trial up to that point. These calls will occur as soon as possible after the completion of the 7-day

surveillance period following each of the first 2 immunizations of cohorts 1 and 2. The first call will thus occur approximately one week before the first immunization with the 25 µg dose level of FMP2.1, and the second will occur approximately one week before the first immunization with the 50 µg dose level (Figure). The purpose of these conference calls will be to review the accumulated safety data to advise whether or not the study can proceed with the dose escalation, and whether the trial can proceed generally. In the event that the DSMB identifies a safety concern, the collaborative group including the investigators, DMID, WRAIR, GSK and USAID will review all safety data to decide whether to give the next sequential dose. Senior investigators and representatives from USAMMDA, DMID, WRAIR, GSK and USAID will be invited to but not obligated to participate in the conference calls during open sessions, which will be followed by closed sessions including only DSMB members.

[figure not shown]

**Figure.** Timeline for safety reviews by DSMB. Arrows down indicate immunization safety data included in safety review. Arrows up indicate review results in recommendation to proceed with immunization.

The DSMB will meet after the 7-day surveillance period following the last immunization of cohort 3 to review safety data and provide advice to the sponsors and investigators with regard to dose selection for the subsequent Phase 2 trial.

The investigator will inform the DSMB of:

- All subsequent protocol amendments, informed consent form changes or revisions of other documents originally submitted for review
- Serious adverse events (SAEs), grade 3 adverse experiences and grade 2 abnormalities of laboratory tests occurring during the study, regardless of relationship to the study vaccine
- New information that may affect adversely the safety of the subjects or the conduct of the study.

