### 12.1 Primary endpoints

- Occurrence of solicited symptoms during a 7-day surveillance period after vaccination (day of vaccination and study days 1, 2, 3 and 7).
- Occurrence of unsolicited symptoms during a 30-day surveillance period after vaccination.
- Occurrence of serious adverse events during the study period.

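### Table 11 gives no intensity grade to injection-site erythema above 20 mm and up to 50 mm, and grades limitation of arm motion as solicited although section 10.2.4 does not list it

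*Protocol*

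**What the plan says.** Section 10.3 presents its scale as "Table 11. Assessment of Solicited Adverse Event (AE) Intensity". The erythema row runs from "Erythema at injection site | 0 | Absent" through Grade 1 (below 5 mm) and Grade 2 (5 to 20 mm) to Grade 3 (above 50 mm). The swelling row just above it has the same Grades 1 and 2, but its Grade 3 begins above 20 mm. The generic intensity scale in the same section has a limited scope: "For all other adverse events than those in Table 11, maximum intensity will be assigned to one of the following categories".

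Table 11 also has a row for "Limitation of arm motion". The local solicited list in 10.2.4 begins with "Pain or tenderness at injection site" and adds only swelling and erythema. The general list has fever, drowsiness, loss of appetite, vomiting and irritability. Section 10.2.5 treats as unsolicited any reported event that is not on those lists.

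The solicited primary endpoint in 12.1 is "Occurrence of solicited symptoms during a 7-day surveillance period after vaccination (day of vaccination and study days 1, 2, 3 and 7"). Intensity is used elsewhere. Section 12.5.3 tabulates it per symptom, group and vaccine administration. Section 5.4.3 says: "Severe (i.e., Grade III) local reactions will be evaluated to determine whether or not further study immunizations should be administered". Section 10.11 has the investigator inform the DSMB of "Serious adverse events (SAEs), grade 3 adverse experiences and grade 2 abnormalities of laboratory tests occurring during the study".

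**The concern.** A grading scale has to assign one grade to every size that can be measured. The erythema row does not. An assessor who measures 30 mm finds it too large for Grade 2 and too small for Grade 3, and no rule in the protocol settles the matter. The grade is assigned at the visit, while dosing is under way. Different assessors may therefore resolve it differently, and the choice decides whether the child's reaction is evaluated as Grade III before the next dose and reported to the DSMB. It also shifts the intensity table, and section 2.4.8 makes reactogenicity one of the grounds for choosing the dose.

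The arm-motion conflict concerns classification. Whether the event is solicited decides three things:

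- whether staff ask about it systematically;
- whether it falls under the 7-day solicited or the 30-day unsolicited endpoint;
- whether it is taken as vaccine-related automatically, as 10.4 requires for solicited local reactions, or left to the investigator's judgment.

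**Working it through.** No sample-size or power figure bears on this point. The check sets the scales and lists side by side.

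**Erythema and swelling scales**

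| Grade | Swelling, Table 11 | Erythema, Table 11 | Erythema, adult trial, Table 5 |
|---|---|---|---|
| 0 | absent | absent | 0 mm |
| 1 | < 5 mm | < 5 mm | > 0 to 20 mm |
| 2 | 5–20 mm | 5–20 mm | > 20 to 50 mm |
| 3 | > 20 mm | > 50 mm | > 50 mm |

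Each Table 11 row was applied to every whole millimetre from 0 to 100:

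- Swelling: no ungraded value.
- Erythema: 21 to 50 mm ungraded, which is 50 − 21 + 1 = 30 values. On a continuous scale the gap is 50 − 20 = 30 mm wide, against 20 − 5 = 15 mm for the whole of Grade 2.

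The adult scale has no gap. The paediatric row has the upper bound of Grade 2 from the swelling row and the lower bound of Grade 3 from the adult table. The document does not say whether two scales were merged or one figure was mistyped.

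**Can another rule supply the grade?** No. Erythema is a Table 11 event, so the generic scale is excluded by its own terms. Table 11 also lacks the instruction to record size that stands beside erythema in adult Table 5, so the protocol text does not ensure that grades could be reassigned later.

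**How often might it arise?** In the Malian adult trial, Table 7 shows 1 erythema event in the two FMP2.1 groups (0 at 25 µg, 1 at 50 µg), over 60 + 59 = 119 doses (Table 1). It was Grade 2, which on the adult scale means above 20 mm and up to 50 mm. The documents give no erythema rate for this vaccine in children.

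**Solicited list against Table 11.** Section 10.2.4 lists 8 events (3 local, 5 general). Table 11 has 9 rows. Every listed event has a row, and the only extra row is limitation of arm motion. In Table 7 that event was recorded 4 + 1 = 5 times at 25 µg and 3 times at 50 µg, 8 in all with FMP2.1, and 0 times with rabies vaccine. Its classification could therefore affect the vaccine groups unequally.

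**The case against.** The strongest reply is that the effect is narrow, and much of that stands.

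- **Primary endpoint.** A reader might infer that part of the primary endpoint cannot be scored. Sections 3.2.1, 10.1 and 12.1 do not support this. The endpoint is occurrence, and a 30 mm erythema is plainly present and counts. Only its intensity is undefined.
- **Stopping rules.** A reader might infer that a halting rule fails. No rule in 10.9 uses the grade of a local reaction; the triggers there are serious adverse events. Section 5.4.3 calls for an evaluation and not an automatic stop. The injection site is examined before doses 2 and 3 whatever the grade, and the DSMB also reviews accumulated safety data.
- **Arm-motion scale.** A reader might see a second hole at 120° or above, because Grade 1 stops short of 120°. The natural reading of Grade 0 covers that range. Table 5 uses the same scale, and events were graded on it in adults. The scale is usable; only the classification conflicts.
- **Ascertainment.** It cannot be said that the site will fail to ask about arm motion, since the CRF and SOPs are not shown. A recorded event would still be graded from Table 11. It would also count in the overall 7-day percentage with a local event, because 12.5.3 includes both solicited and unsolicited events there.

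The reply does not remove the gap or the contradiction. All four erythema rows are legible, so this is not a fault of text extraction. Nor can it be left to an analysis plan, because the grade is assigned during dosing and two safety steps depend on it.

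**Conclusion.** The point holds as an internal inconsistency in the safety grading. Erythema above 20 mm and up to 50 mm has no intensity grade. In that band the intensity tabulation, the Grade III evaluation before further immunization and the grade 3 report to the DSMB are undefined. Few children may be affected if erythema is as rare as in the Malian adults, but that is an assumption: the adult figure is a single event, and children may differ.

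Limitation of arm motion is solicited by Table 11 and unsolicited by 10.2.4 with 10.2.5. This leaves open whether it is elicited systematically, which of two primary endpoints it enters, and whether 10.4 makes it related automatically.

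Which erythema bound was intended, and whether arm motion should be solicited, cannot be decided from the document. Both should be settled before the first injection, because a grade or a question missed at the visit may not be recoverable.

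**What to change.** Before the first injection the sponsor should:

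1. Reconcile the 20 mm and 50 mm erythema bounds in Table 11 so that Grades 2 and 3 abut, with every size assigned to exactly one grade.
2. Require erythema size in millimetres on the CRF, so that grades can be recomputed.
3. Reconcile 10.2.4 with Table 11 on limitation of arm motion by listing it in both or in neither, and align the CRF with that choice. Its endpoint window and the causality rule in 10.4 then follow.

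The cost is one table correction, one list correction and a matching CRF edit. No visits are added, and the injection site is already examined at the surveillance visits.
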